## Abstract

**Background:**

The adoption of a healthy lifestyle plays a crucial role for the health and well-being of health care professionals. Previous e- and mHealth interventions relied on deliberative psychological processes (e.g., intention, planning) to target lifestyle changes, while revealing mixed efficacy. The additional potential of non-deliberative, automatic processes (i.e., habits) for behavior change has been understudied in interventions so far. The Habit Coach mHealth intervention combines deliberative and non-deliberative processes to support health care professionals in forming healthy physical activity, nutrition and mindfulness habits in daily life. The aim of this paper is to outline the study protocol including a detailed description of the mHealth intervention, evaluation plan, and study design. The purpose of this trial is to understand healthy habit formation in health care professionals over time.

**Methods:**

A one-arm, multicenter mHealth intervention study will be conducted. Behavioral and psychosocial predictors will be collected via within-app questionnaires across a 100-day period at baseline, post, as well as at weekly assessments. To understand habit formation across time, linear mixed models will be used.

**Discussion:**

This trial aims to unravel the role of motivational and volitional determinants for healthy habit formation across multiple health behaviors in health care professionals embedded in a mHealth intervention.

**Trial registration:**

This trial is registered in the German Clinical Trials Register, DRKS-ID DRKS00027156. Date of registration 17 November 2021.

**Supplementary Information:**

The online version contains supplementary material available at 10.1186/s12889-022-13986-0.

## Background

The tasks of care giving occupations are stressful and emotionally exhausting [1]. At the same time, their work environment exposes them to various hazards ranging from infectious diseases to radiation [2–4] as well as irregular and long work schedules. While long working hours have been positively associated with lower health, including higher body weight [5] and insufficient physical activity [6], meaningful engagement in health protective and promoting activities (e.g., food preparation, exercising) often comes up short [7]. Consequently, there is a strong rationale and need for fostering health promoting behaviors in health care professionals [8].

Besides the importance of the workplace, health care professionals’ individual health behavior plays a decisive role for their health and well-being [9]. Replacing well-established behavioral patterns with healthier alternatives, however, appears per se as challenging, particularly for health care professionals. Behavioral sciences often apply theories to explain individual behavior change, with a preponderant focus on social cognitive theories ([10]; e.g., the social cognitive theory [11], the theory of planned behavior [12] or the transtheoretical model [13]). These models share the common notion that individuals change their behavior as a result of deliberate psychological processes including self-efficacy and intentions. Meta-analytical evidence on the efficacy of behavioral interventions, however, revealed only short-term behavior changes, and mainly for those interventions that incorporated deliberate, self-regulation techniques such as planning, self-monitoring and feedback provision [14]. As such, while behavioral interventions based on traditional social cognitive models show promising results, there still remains room to expand upon different theoretical angles to change behavior [15, 16].

### Understanding habit formation and its predictors

More recently non-conscious, automatic processes, such as habits, received credit in the behavior change literature [17, 18]. *Habits* can be defined as process by which a stimulus automatically creates an impulse towards action, based on learned stimulus–response associations[19, 20]. The traditional perspective of habit formation implies repetition of an intended behavior in a stable context [21, 22], to the extent that after sufficient repetition, the intended behavior will be elucidated by cues in the environment rather than through an ongoing and conscious decision making process [23].

In line with these advancements, several attempts have been undertaken to identify strategies that could facilitate and support the formation of healthy habits. Gardner & Lally [24] developed a framework to aid the conceptual organization of antecedents of the habit formation process, proposing the categorization of determinants into stages, much like in well-established stage models of behavior change (e.g., health action process approach, HAPA, [25]). In the first stage, the motivational stage (1), people need to come to a decision to perform a new behavior (Fig. 1). Deliberation over action and potential consequences result in intention formation. In the following volitional stage (2), people attempt to translate their intentions into action. Individuals need to make use of self-regulation strategies to initiate action. In the third stage (3a), people need to repeat the new behavior, which requires sustained motivation and self-regulation skills. At the final stage (3b), the intended behavior is repeated in a way to support the development of habit associations. While stage 3a is per se about behavioral repetition, 3b emphasizes the strengthening of cue-response associations. Together both stages culminate in the formation of a new habit.

**Fig. 1 Fig1:**
[figure not shown]
Theoretical framework for the present study based on Schwarzer [25] and Gardner and Lally [26]

Building on this integrated framework, outcome expectancies and self-efficacy beliefs complement the process of intention formation (stage 1). Indeed, before a new behavior becomes automatic, individuals need to set a specific behavioral *goal* (e.g., exercising more, eating healthier). Although the latter initially requires discipline and memory performance it should—over time—become habitual after sufficient repetition of the behavior. Goals have been shown to be important antecedents of action initiation [27]. Individuals most likely form a goal when they anticipate positive consequences as a result of their intended behavior (i.e., outcome expectancies) and feel capable to perform the intended behavior despite barriers (i.e., self-efficacy, [28]). While *outcome expectancies* refer to the perceived physical, affective (self-evaluative) and social consequences of one’s behavior, *self-efficacy* is defined as the ability to control one’s behavior to produce desired outcomes [25]. In terms of intervention strategies, information provision on beneficial consequences of action or letting individuals choose behaviors they feel confident about to execute, set the stage for the formation of habits by establishing a motivational basis [29]. Moreover, research has shown that context-dependent repetition was most likely when individuals formulated goals that were specific, achievable and realistic [30]. In contrast, low quality self-chosen goals that were vaguely defined, specified numerous behaviors, and failed to identify a context for action were suboptimal for habit formation [31, 32].

To foster action initiation (stage 2), self-regulation strategies such as *planning* come into play [33]. Planning helps people to act in favorable situations. By anticipating contexts suitable for behavioral execution in addition to planning how the behavior will be performed in a given context, facilitates developing cue-behavior associations as indicated in stage 3b [24, 34]. As a special form of planning, action planning describes a process in which a person determines specifically when, where and how an intended behavior will be executed. While health care professionals who make use of planning are more likely to engage in health promoting behaviors [35, 36], the underlying processes why and how they build a habit as a result are less clear. Presumably, planning makes a specific cue more easily available in memory so that when exposed to the cue, people are more likely to remember and execute the behavior [27]. As soon as an action plan has been formed, the intended behavior is more likely to be triggered automatically by the contextual cue rather than by a deliberative weighing of pros and cons [37].

Lastly, *self-monitoring* of goals presents an additional facilitative self-regulatory strategy conducive to action control (i.e., the control of self-regulation and voluntary action), where the behavior is continuously monitored and evaluated with respect to a behavioral standard [38]. While self-monitoring has been proven to be a valuable component of behavior change interventions to reduce sedentary behavior [39], its supportive role in the habit formation process (i.e. increasing automaticity of a new health behavior) has been shown across various health behaviors, such as diet and physical activity ([40–42]; for a literature review see [29]).

Some habit formation prerequisites, such as goal setting, action planning and self-monitoring, have been shown to support behavior change (e.g., physical activity [43];), also in worksite interventions [44]. Findings from systematic reviews of traditional worksite based lifestyle interventions, however, indicated mixed findings, showing that 40% to 45% of the included intervention studies did not reveal positive effects on physical activity [45, 46]. Lack of intervention effects was mainly attributed to insufficient theoretical behavioral change rationales of interventions [45] as well as high costs and disruption of the working day [47], with the latter most likely preventing program implementation in the first place [48]. Therefore, there is a need for brief evidence- and theory-based interventions that are feasible to be implemented throughout a busy workday.

Delivering behavioral interventions via electronic health (eHealth) or mobile health (mHealth) technology might overcome aforementioned implementation problems. Still, research investigating the efficacy of digital interventions (i.e., e- and mHealth) presented mixed results: while evidence exists that points to the effectiveness of e- and mHealth interventions in promoting physical activity (for a meta-analysis in adults see Laranjo et al., [49]) and healthy eating in people with non-communicable diseases [50, 51], other reviews report positive – albeit highly variable and often small effects on behaviors such as physical activity, exercise and tobacco use [52, 53]. Mixed mHealth effectiveness was ascribed to poorly described theoretical backgrounds and behavior change techniques, as well as uncertainties about effective dosage and delivery modes [54–56]. Taken together, this lack of clarity explains why researchers frequently start from scratch when developing new intervention programs. Publications of study protocols that precisely describe the active ingredients (i.e., mechanisms of action), dose and mode of the interventions are therefore required [57].

### Objectives

The present study outlines the protocol for a longitudinal, multicenter single-arm study among health care professionals investigating the role of theory-based motivational and volitional predictors for healthy habit formation in daily life based on a mHealth intervention targeting physical activity, healthy nutrition and mindfulness behaviors (i.e., engaging in mindfulness techniques and relaxation exercises). The aim of this paper is to outline the study protocol including a detailed description of the mHealth intervention, the evaluation plan, and the study design. The main purpose of this trial is to understand the habit formation process for physical activity, nutrition and mindfulness behaviors and its predictors. As preliminary hypothesis (hypothesis 1 a-e), we expect to find positive changes from baseline to post assessments (i.e., 100 days post baseline) in: a) habit strength, b) motivational constructs (i.e., intention, outcome expectancies, self-efficacy), c) volitional constructs (i.e., action planning), d) health behavior (i.e., physical activity, nutrition, mindfulness behaviors) and e) health status (i.e., stress, back pain, well-being, physical and psychological health, body mass index). For the primary endpoint (habit strength over time) and to understand predictors of habit formation over time, we hypothesize that a) habit strength at post-assessment is predicted by baseline motivational and volitional constructs, controlling for baseline habit strength (hypothesis 2), b) that health behavior and c) health status at post assessment are predicted by motivational and volitional constructs as well as habit strength at baseline (hypotheses 3 and 4, respectively). Finally, we hypothesize that next-week habit strength will show positive associations with behavior-related motivational (5a) and volitional constructs over time (5b).

Additionally, we conduct a process evaluation by evaluating participants’ experiences and satisfaction with the app. For the process evaluation a mixed-methods approach will be applied involving questionnaires and structured interviews. The items addressed in this protocol paper are based on the 2013 Standard Protocol Items: Recommendations for Interventional Trials (SPIRIT) statement [[58]; see Additional file 1].

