##### Automaticity

Automaticity is assessed with four items by means of the subscale Self-Report Behavioral Automaticity Index from the Self Report Habit Index (SRHI) [65, 66] at baseline and post assessments, and with two items at interim assessments (due to economic reasons). Following the stem “Physical activity/ Eating five portions fruit and vegetables/ Practicing mindfulness activities three times per week for ten minutes … is something” participants indicate on a five-point Likert scale ranging from 1 (do not agree) to 5 (totally agree) if they engage in the behaviors for example “automatically”. The SRHI has proven to be a reliable and valid instrument to measure habit strength for physical activity (α = 0.96) [66].

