### Statistical analysis

Statistical analysis will be performed using SPSS Version 27 and conducted after completion of the data collection process. Interim analyses will not be performed. All primary outcome data will be screened for normal distribution by using the Shapiro–Wilk test. Data will be checked for outliers and missing data. Descriptive statistics will be run to explore the sample characteristics. Continuous variables will be presented as means and standard deviations, while categorical variables will be displayed by percentages of participants in each possible category. Intention-to-treat analyses will be conducted, given that drop-out rates are usually high in eHealth research [80], per protocol analysis are not feasible. Only data sets from participants who completed the baseline, post and 50% of the weekly assessments will be included in the analysis. To investigate difference between the sample of analysis and those who provided baseline data only, differences between baseline scores and a dichotomous attrition variable (i.e., 0 = not retained for analysis, 1 = retained) will be analyzed using χ^*2*^ and *t*-tests, followed by logistic regressions. To test for changes in habit strength, motivational (intention, self-efficacy, and outcome expectations), volitional constructs (action planning), health behaviors and health status from baseline to post assessments, analysis of variance with repeated measures and *t*-tests between subsequent measures will be run (hypothesis 1 a-e). To examine hypotheses 2–4, hierarchical multiple linear regression analyses will be conducted, with motivational, volitional and habit-related predictors at baseline to predict habit strength, health status and health behavior at post-assessment. To account for the hierarchically structure of data (i.e., repeated measurements nested within individuals) we plan to run two-level models with 13 assessment periods nested in participants (hypotheses 5 a-b, linear mixed models, LMM, [81]). LMM allows to test for simultaneous assessment of the effects of within-person variation in weekly assessments of behavior,habit strength and predictor variables (level 1) and between-person variables such as age, health status and other covaraites measured only once (level 2). Prior to running analyzes, the time parameters will be grand mean centered to minimize multicollinearity. Subsequently, various steps will be undertaken to determine appropriate model fit, as suggested by Field [81]. Once the model shows appropriate fit parameters, LMM can be conducted by selecting the Restricted Maximum Likelihood for estimation method [81]. In a model including all behavior-related cognitions and covariates simultaneously, motivational and volitional variables will be modeled at the between-person level (e.g., comparing persons with higher average versus lower average intentions) and the within-person level (e.g., assessments when intentions to engage in health behavior were higher-than-usual vs. lower-than-usual). Models will be run separately for each behavioral domain.

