### Strengths, challenges and limitations

Strengths. The mHealth intervention is theory driven and provides support during the entire behavior change process, starting with a motivational (i.e., goal setting), over a volitional (i.e., action planning) to habit formation and behavioral maintenance phase. Although mHealth interventions intended to increase physical activity and eating behaviors have shown positive effects, these effects often times were small and highly variable, caused by insufficient description of theoretical foundations and behavior change techniques used. The present study focuses specifically on mechanisms of action and respective behavior change techniques in order to predict change in behavior and make intervention design and evaluation more transparent and replicable. Furthermore, by allowing health care professionals to integrate the within-app mini interventions into their daily (work) routine, it is intended to tackle commonly reported problems of implementing programs such as massive disruption of the working day and attrition based on problems to fit interventions into daily routines outside the work context.

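### Hypotheses 3 and 4 use only pre-programme habit and do not name the baseline outcome as a covariate, so a positive habit coefficient may reflect nothing more than stable prior behaviour

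*Protocol article*

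**What the plan says.** The Objectives section states that health behaviour and health status at post-assessment are "predicted by motivational and volitional constructs as well as habit strength at baseline" (hypotheses 3 and 4). The Statistical analysis section assigns hierarchical multiple linear regression to hypotheses 2 to 4, "with motivational, volitional and habit-related predictors at baseline to predict habit strength, health status and health behavior at post-assessment". The two places agree, so this is a settled choice and not a slip of wording.

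Hypothesis 2 is worded differently: "habit strength at post-assessment is predicted by baseline motivational and volitional constructs, controlling for baseline habit strength (hypothesis 2". It names its baseline control. Hypotheses 3 and 4 do not.

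Habit measured after baseline appears only as an outcome:
- Hypothesis 1: "we expect to find positive changes from baseline to post assessments", tested for each construct separately, with no link between them.
- Hypothesis 2: post-assessment habit strength is the outcome.
- Hypothesis 5: "next-week habit strength will show positive associations with behavior-related motivational (5a) and volitional constructs over time (5b".
- The Discussion overview treats change in habit strength as something to be predicted.

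Later habit data do exist. The Automaticity section gives four items at baseline and post, "and with two items at interim assessments". The Evaluation design section places the interim assessments at booking date + 28 and + 56, ahead of the post assessment at + 99.

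**The concern.** The abstract motivates the study with the statement "The additional potential of non-deliberative, automatic processes (i.e., habits) for behavior change has been understudied in interventions so far", and the strengths section says the study "focuses specifically on mechanisms of action and respective behavior change techniques in order to predict change in behavior". Hypotheses 3 and 4 are the only ones in which habit predicts behaviour or health, so readers of the results will look there for evidence on habit.

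Two features weaken what these regressions can say. First, habit at booking date + 0 precedes every component of the app, so it measures habit that the programme did not produce. Second, habit and behaviour are correlated at entry and behaviour is fairly stable over 100 days. Unless the baseline outcome is in the model, baseline habit stands in for baseline behaviour, and a positive coefficient is expected even if habit contributes nothing further. That coefficient could be reported as support for a role of habit in behaviour change when it shows only persistence. If those with weak initial habits gain most, a real benefit of newly formed habit would lower the coefficient and could be read as evidence against habit.

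**Working it through.** The plan gives no figure to reproduce here. The check is an illustration in which every effect size is an assumption. The sample is 160, because 228 × (1 − 0.30) = 159.6 if the stated 228 is read as including 30% attrition.

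**Model.** Baseline habit H0 has mean 0 and SD 1. Baseline behaviour is B0 = 0.5·H0 + noise. Habit gain is G = 0.5 − λ·H0 + noise (SD 0.7). Post behaviour is B1 = 0.7·B0 + β·G + noise. β is the effect of newly formed habit; λ is how much more people with weak initial habits gain.

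**Step 1: expected coefficient of H0.**
- As worded in the plan (B0 not in the model): 0.7 × 0.5 − λβ = 0.35 − λβ.
- With B0 in the model: −λβ.

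| λ | β | Planned: 0.35 − λβ | With B0: −λβ |
|---|---|---|---|
| 0 | 0 | 0.35 | 0.00 |
| 0 | 0.3 | 0.35 | 0.00 |
| 0 | 0.6 | 0.35 | 0.00 |
| 0.3 | 0 | 0.35 | 0.00 |
| 0.3 | 0.3 | 0.26 | −0.09 |
| 0.3 | 0.6 | 0.17 | −0.18 |

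Simulation agrees. With β = 0 the planned coefficient averages about 0.35 and is significant in about 99% of runs; with B0 added it averages about 0.00 with 5 to 6% rejection. The 0.35 is entirely the product of stability (0.7) and the baseline association (0.5).

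**Step 2: a second model.** This one includes baseline motivation, a direct habit-behaviour path of 0.4, stability of 0.5, and a correlation ρ between baseline habit and habit change (both with SD 1). The planned coefficient is 0.5 × 0.4 + ρβ = 0.20 + ρβ. With no effect of formed habit it is 0.20. With β = 0.4 it is 0.20 for ρ = 0, 0.20 − 0.12 = 0.08 for ρ = −0.3, and 0.20 − 0.20 = 0.00 for ρ = −0.5. The pattern is the same.

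**Step 3: what day-56 automaticity would add.** Let H56 = H0 + 0.7·G + noise (SD s), and add it to H0 and B0. Given those two, its coefficient is β × (0.7 × 0.49)/(0.49 × 0.49 + s²) = β × 0.343/(0.2401 + s²).

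| s | β = 0 | β = 0.3 | β = 0.6 |
|---|---|---|---|
| 0.1 | 0 | 0.41 | 0.82 |
| 0.3 | 0 | 0.31 | 0.62 |
| 0.5 | 0 | 0.21 | 0.42 |
| 0.7 | 0 | 0.14 | 0.28 |

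Under this model the block is zero when there is no effect and positive when there is one. Its size depends on measurement noise, and a noisy two-item score could show half the effect or less.

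**Step 4: the reverse path.** The Background section on understanding habit formation says that repetition of behaviour builds habit. Set the effect of habit on behaviour to zero and let day-56 behaviour build habit: B56 = 0.7·B0 + noise (SD 0.7), H56 = 0.7·H0 + a·B56 + noise (SD s), B1 = 0.7·B56 + noise. Given H0 and B0, the coefficient of H56 is 0.7 × 0.49a/(0.49a² + s²) = 0.343a/(0.49a² + s²).

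| a | s = 0.5 | s = 0.6 |
|---|---|---|
| 0.2 | 0.25 | 0.18 |
| 0.3 | 0.35 | 0.25 |
| 0.5 | 0.46 | 0.36 |

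For the weaker set (0.18, 0.25, 0.36), 37%, 66% and 96% of 2,000 simulated trials were significant although habit had no effect. In this model B1 depends on the past only through B56, so adjusting for B56 brings the expected coefficient of H56 to zero. An imperfect measure of B56 would do so only in part.

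**The case against.** The best reply is that hypotheses 3 and 4 openly ask a baseline-prediction question, which is legitimate. The declared main purpose is to understand habit formation and its predictors, and the primary endpoint is habit strength over time. Nowhere does the article say that hypotheses 3 and 4 test whether newly formed habits change behaviour. The limitations section concedes that effectiveness cannot be evaluated without a control group, and the sentence on mechanisms of action fits the table of behaviour change techniques at least as well as it fits these regressions. All of this stands. It limits the point to secondary hypotheses and to interpretation, but does not supply the missing covariate.

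It may also be said that covariates belong in a fuller analysis plan. That has some force. But the article names the baseline control for hypothesis 2 and words hypotheses 3 and 4 without one, so as written they differ.

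The mixed models do include weekly behaviour and habit strength at level 1. They serve hypotheses 5a and 5b, in which next-week habit is the outcome, so they do not fill the gap.

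Two stronger readings are tempting. A reader might infer that hypotheses 3 and 4 give the same answer whether or not formed habits matter. That holds only if gains are unrelated to baseline habit (λ = 0); otherwise the coefficient shifts, though downwards as the true benefit rises. On a bounded 1 to 5 scale some dependence is plausible. A reader might also infer that day-56 automaticity would provide the missing test of the habit mechanism. Step 4 shows that it would not.

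**Conclusion.** The point holds in a limited form. As worded, hypotheses 3 and 4 cannot separate a contribution of habit from persistence of prior behaviour or health, and they are silent on habit formed during the programme. Under the assumed stability of 0.7 and baseline association of 0.5, the whole planned coefficient of 0.35 is persistence, and it is almost always significant at 160 completers. The sizes rest on those assumptions, since the article gives no correlations. The direction needs only that habit and outcome are positively related at entry and that the outcome is reasonably stable.

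The documents do not support calling the analysis invalid for its stated baseline-prediction question, nor saying that the trial fails its main purpose. The primary endpoint and hypotheses 2 and 5 are untouched. The change is worth making before analysis because it is cheap and prevents a predictable misreading.

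**What to change.** 1. In the hierarchical regressions for hypotheses 3 and 4, enter the baseline value of the outcome in the first block, as hypothesis 2 already does for habit.
2. State that the baseline-habit coefficient concerns pre-existing habit only.
3. Add a final block, labelled secondary or exploratory, with automaticity at + 56. Score baseline automaticity on the same two items and keep it in the model. Where available, also adjust for behaviour frequency up to + 56 from the weekly self-monitoring item.
4. Report that block as an association between habit gained and later behaviour or health, not as a test of the habit mechanism, because repetition itself builds habit and the study has one arm.

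The cost is analysis wording, with no new data collection. The Ethical approval section records that hypotheses were already refined by a registry amendment and that further changes will be reported, so a route exists. There are three downsides. A two-item score is noisier, and the article does not say which two items are used at interim, so this must be confirmed. Some included participants may lack the + 56 form, since the inclusion rule asks for only half of the weekly assessments, and this needs a stated rule. The self-monitoring item counts days of practising favourite exercises, so it stands in only partly for the behaviours measured at post-assessment.
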